# The gametocytocidal efficacy of primaquine in malaria asymptomatic carriers treated with dihydroartemisinin-piperaquine in The Gambia (PRINOGAM): study protocol for a randomised controlled trial

**DOI:** 10.1186/s13063-015-0597-1

**Published:** 2015-03-01

**Keywords:** Malaria, Plasmodium falciparum, Asymptomatic infection, Gametocyte, Primaquine, Safety, Efficacy, Elimination

## Abstract

**Background:**

Finding efficacious tools to decrease and interrupt malaria transmission is essential to sustain the gains in malaria control and contain the emergence of artemisinin resistance. Primaquine is effective against *Plasmodium falciparum* gametocytes and recommended for treatment campaigns in (pre-)elimination settings. Safety concerns preclude its use in endemic African countries with variable proportions of glucose-6-phosphate dehydrogenase (G6PD)-deficient individuals. The efficacy of the current recommended dose needs to be evaluated, particularly in individuals with an asymptomatic malaria infection.

**Methods/design:**

This is a four-arm, open label, randomized controlled trial that aims to determine and compare the effect of three different single doses of primaquine combined with dihydroartemisinin-piperaquine, an artemisinin-based combination therapy, on gametocyte carriage in asymptomatic, malaria infected, G6PD-normal individuals. Approximately 1,200 participants are enrolled and followed for 42 days, with the primary endpoint being the prevalence of *Plasmodium falciparum* gametocyte carriage at day 7 of follow-up determined by quantitative nucleic acid sequence based amplification assay. Direct membrane feeding experiments to determine infectiousness to mosquitoes are conducted as a biological secondary endpoint.

**Discussion:**

Sub-Saharan Africa, with a relatively high but poorly characterized G6PD prevalence, could potentially benefit from the use of primaquine to further reduce or interrupt malaria transmission. However, G6PD screening may not be feasible given the cost and difficulties in interpreting test results in terms of risk of haemolysis. Because the haemolytic effect of primaquine is dose-dependent, determining the minimal gametocytocidal and transmission-blocking dose of primaquine is extremely important to help address public health concerns over its safety and validate the efficacy of lower than recommended dosages. By including infectiousness to mosquitoes, the trial provides complementary evidence for the potential of the drug to interrupt transmission to mosquitoes.

**Trial registration:**

ClinicalTrials.gov: NCT01838902 (12 April 2013).

## Background

The scale-up of anti-malaria interventions, including artemisinin-based combination therapy (ACT), and the subsequent decline in many malaria indicators has boosted prospects of local or regional malaria elimination [1]. However, it is evident that additional tools, including drugs effective against sexual (gametocyte) stages and programmes that are targeted at asymptomatic parasite carriage, would be needed if the goal of interrupting *Plasmodium falciparum* malaria transmission were to be achieved.

A number of endemic countries, including some in sub-Saharan Africa, have achieved substantial reductions in their malaria burden [1,2] and are considering the possibility of eliminating malaria within their borders. Artemisinin derivatives are extremely effective against both asexual and early-stage *P. falciparum* gametocytes and less so against mature gametocytes [3,4]. Combining ACTs with primaquine (PQ), an 8-aminoquinoline effective against mature gametocytes, targets all parasite stages and thus can halt the transfer of gametocytes from humans to mosquitoes. In this context, PQ could play an essential role in interrupting transmission but there are concerns, especially over its safety and efficacy, that could preclude its large-scale use in these countries.

The optimal PQ dose used in combination with an ACT against *P. falciparum* gametocytes has been the subject of some discussion. Previously recommended by the World Health Organization as a single 0.75 mg base/kg, it was recently revised to 0.25 mg base/kg as this dose was unlikely to result in serious toxicity, especially in individuals with any glucose-6-phosphate dehydrogenase (G6PD) deficiency variant, while retaining its gametocytocidal effect [5]. Whereas the 0.75 mg base/kg PQ dose had a variable impact on transmission [6,7], the efficacy of the 0.25 mg base/kg has not been evaluated in any recent trial.

A recently concluded dose-ranging trial of PQ plus artemether-lumefantrine in children with uncomplicated malaria showed that a 0.4 mg/kg dose was as efficacious as the 0.75 mg/kg dose in clearing gametocytes [8]. The trial excluded phenotypically G6PD-deficient individuals by fluorescent spot test and observed no clinically relevant haemolysis, although a statistically significant haemolytic effect was observed in phenotypically G6PD-sufficient but genotypically G6PD-deficient individuals receiving 0.75 mg/kg or 0.4 mg/kg PQ [9].

The dynamics of gametocyte carriage may differ considerably between symptomatic and asymptomatic infections and these differences in gametocyte dynamics may explain why previous studies in Africa have reached different conclusions on the added value of PQ in symptomatic and asymptomatic infections [7,10]. Although the acute phase of clinical malaria attacks have been associated with a subsequent wave of gametocytes that may persist longer after treatment [11], asymptomatic individuals typically have lower densities of both asexual and sexual parasites yet potentially have more mature gametocytes as a result of the long duration of asymptomatic parasite carriage [12]. Because asymptomatic infections typically comprise the majority of malaria infections in populations [13], studies in asymptomatic parasite carriers are needed to provide complementary evidence for the efficacy and safety of even lower PQ doses.

This study combines gametocyte carriage measured using molecular detection methods [10,14] with a complementary biological endpoint of gametocyte infectivity in a sub-group of study subjects to assess the transmission blocking effect of PQ [15].

### Trial objectives and endpoints

The trial aims to determine and compare the effect of three different single doses of PQ combined with an ACT, dihydroartemisinin-piperaquine (DHA-PPQ), on gametocyte carriage in asymptomatic, malaria-infected, G6PD-normal individuals. In addition, it will determine and compare the effect of the above combinations on change in haemoglobin concentration during follow-up, infectiousness to mosquitoes, parasite clearance time and cure rate.

The main trial endpoint is the prevalence of *P. falciparum* gametocyte carriage at day 7 of follow-up determined by quantitative nucleic acid sequence based amplification assay (QT-NASBA).

Other endpoints include: 1) the prevalence of *P. falciparum* gametocyte carriage, determined by QT-NASBA, during other follow-up visits; 2) change in haemoglobin values between enrollment (day 0) and each day of follow-up; 3) infectiousness to mosquitoes on day 7 determined by direct membrane feeding assay (DMFA); 4) proportion of participants with recurrent infections (polymerase chain reaction adjusted and unadjusted) after day 7; and 5) the prevalence of adverse events and serious adverse events.

## Methods

### Design

This is a four-arm, open label, randomized controlled trial in which G6PD-normal asymptomatic *Plasmodium falciparum*-infected individuals identified through population screening are randomized to receive either a complete course of DHA-PPQ alone (control) or a course of DHA-PPQ plus one of three different doses of PQ (intervention): 0.75 mg base/kg, 0.4 mg base/kg and 0.2 mg base/kg, given as a single dose.

### Study area and participant selection

Participants are recruited from villages around the Medical Research Council’s field stations in the Central and Upper River Regions in The Gambia. Malaria transmission in the country is well described, and characterized by marked seasonality with a peak between September and November [16]. Participants are selected in a two-stage screening process. An initial pre-screening is used to determine infection (rapid antigen test kit) and establish a baseline parasitaemia (microscopy). Individuals aged 1 year and above with parasite density ≥20 parasites/μl are invited to the base clinic the following day where, after a written informed consent, they undergo screening for G6PD status (N Dimopoulos SA, Greece), haemoglobin measurement (Hemocue, Ängelholm, Sweden) and, if eligible, are enrolled (Figure 1). Infected but ineligible persons are treated with a full course of artemether-lumefantrine. In addition, those with haemoglobin counts <8 g/dl receive iron supplements while G6PD-deficient individuals will be counselled on their test results and provided with a notification card indicating their G6PD status which they are advised to present at clinics when seeking medical care.

**Figure 1 Fig1:**
[figure not shown]
**DHA-PPQ, dihydroartemisinin-piperaquine; DMFA, direct membrane feeding assay; Hb, haemoglobin; G6PD, glucose-6-phosphate dehydrogenase; PCR, polymerase chain reaction; PQ, primaquine; RDT, rapid diagnostic test.**

### Randomisation and blinding

Enrolment into the trial arms follows a randomisation scheme in a 1:1:1:1 ratio using blocks of varying size to ensure a balance in recruitment between the four groups. A randomisation list, generated by the trial statistician using Stata software version 13 (Stata Corp. College Station, TX, USA), is sent to a physician not involved in the trial who puts the codes for the allocation groups into sequentially numbered, opaque envelopes. The envelopes are opened by the clinic team only after the potential participant meets the eligibility criteria.

This is an open-label trial; staff involved in clinical care, including administering the trial drugs, are aware of the assigned groups but those involved in sample processing and data analysis are blinded.

### Treatment and follow-up

All participants in the trial will receive a complete 3-day course of DHA-PPQ based on body weight according to the manufacturer’s instructions. DHA-PPQ is available as both paediatric (dihydroartemisinin 20 mg/piperaquine 160 mg) and adult (dihydroartemisinin 40 mg/piperaquine 320 mg) formulations. Participants in the three intervention arms are randomized to receive a single 0.75 mg/kg, 0.40 mg/kg or 0.20 mg/kg dose of PQ base on day 2 with the third dose of DHA-PPQ. Each tablet of PQ contains 15 mg base and, to ensure the accuracy of doses <15 mg, the tablet will be reconstituted in 15 ml water to achieve a 1 mg/ml concentration and the required dose dispensed using a sterile syringe. A nurse directly observes all treatments and treatment may be repeated once if a participant vomits any of the drugs within 30 minutes of being administered.

Each participant attends eight scheduled follow-up visits on days 3, 7, 10, 14, 21, 28, 35, and 42 for clinical evaluation and blood sampling. Blood samples from a finger prick are collected for gametocyte (QT-NASBA) and asexual parasite clearance (microscopy and polymerase chain reaction) and haemoglobin measurement. Additional tests may be requested during unscheduled visits to the clinic (Table 1). Thick blood films stained with 10% Giemsa for 10 minutes are examined under 1000-fold magnification by trained microscopists. Asexual parasite density is determined by counting the number of asexual parasites per white blood cell (WBC) until 500 WBCs have been counted (assuming a mean WBC count of 8,000/μl) and results presented as parasites/μl.

**Table 1 Tab1:** **Trial activity on scheduled visit days**

**Day**	**−1**	**0**	**1**	**2**	**3**	**7**	**10**	**14**	**21**	**28**	**35**	**42**
Village screening (RDT+ slide)	X											
Informed consent for the trial		X										
G6PD test	X											
Clinical review (history and examination)		X			X	X	X	X	X	X	X	X
Temperature, pulse		X		X	X	X	X	X	X	X	X	X
Weight		X										
Thick blood film		X	X	X	X	X	X	X	X	X	X	X
Haemoglobin, PCR (filter paper)		X			X	X	X	X	X	X	X	X
Gametocytaemia (QT-NASBA)		X			X	X	X	X		X		X
Adverse events		X	X	X	X	X	X	X	X	X	X	X
Treatment		X	X	X								
Direct membrane feeding assay						X						

G6PD, glucose-6-phosphate dehydrogenase; PCR, polymerase chain reaction; QT-NASBA, quantitative nucleic acid sequence based amplification assay; RDT, rapid diagnostic test.

### Quantitative nucleic acid sequence based amplification assay

The primary endpoint of the trial is the prevalence of gametocytes measured by molecular methods on day 7 of follow-up. The detection and quantification of gametocytes is by real-time QT-NASBA which is based on stage-specific gene expression of Pfs25 mRNA by parasites. QT-NASBA is a high throughput technique suited to detecting mature gametocytes with a sensitivity of 0.01 to 0.1 gametocytes/μl blood [17]. It is based on the activities of three enzymes: Reverse transcriptase, T7 RNA polymerase and RNase H and target-specific forward and reverse primers, which includes a T7 polymerase promoter sequence, for continuous and direct amplification of RNA molecules in a single mixture at an isothermal temperature of 41°C. Real-time gametocyte detection and quantification is by a fluorescent-labelled molecular beacon with a sequence complementary to those of amplified anti-sense RNA molecules.

RNA is extracted manually from 50 μl of blood stored in RNAlater using commercial lysis buffers (Severn Biotech, Kidderminster, Worcestershire, UK) and previously described methods that involve nuclease inactivation and nucleic acid binding [18]. Gametocyte density is calculated in relation to the standard gametocyte stage V dilution series using the time point of amplification at which the fluorescence detecting target amplicons exceed the mean fluorescence of three negative controls + 20 standard deviations [17]. Standard curves for density quantification are generated using trend lines of known quantities of gametocytes from laboratory-cultured NF54 parasite strains.

### Direct membrane feeding assay

To measure biological evidence of gametocyte clearance, a subset of 100 participants from each arm will be randomly selected for direct membrane feeding experiments on day 7 using a published protocol [19]. In summary, 3 ml of blood are collected from the participant’s arm and 500 μl is added to two glass feeders and fed to about 100 locally reared 4- to 5-day-old female *Anopheles gambiae sensu stricto* mosquitoes through an artificial membrane. The setup is maintained at 37°C by a temperature controlled water bath and, after 15 minutes of feeding, fully fed mosquitoes are transferred into a holding cage maintained at 27 to 29°C and sustained on 5% glucose for 7 days while partially fed and unfed ones are destroyed. Mosquitoes that survive to this period are dissected in 0.5% mercurochrome, and their midguts examined for oocyst prevalence and density. The proportion of infected mosquitoes, the number of infected mosquitoes divided by the total number of examined mosquitoes, and the density of oocysts in infected mosquitoes is presented.

### Sample size considerations

The sample size was calculated to detect a difference in gametocyte prevalence on day 7 after treatment, between the control (DHA-PPQ only) and 0.75 mg/kg PQ arm, and between this and lower doses of PQ (0.4 mg/kg and 0.2 mg/kg). Two hypotheses underscore the sample size calculation: 1) treatment with PQ (any dose) and DHA-PPQ results in significantly lower gametocyte carriage compared to treatment with DHA-PPQ alone; and 2) a single dose of 0.4 mg base/kg or 0.2 mg base/kg PQ administered with the last dose of DHA-PPQ has similar gametocytocidal efficacy as a single 0.75 mg base/kg dose.

For the first hypothesis, the underlying assumption is that, although a substantial proportion of asymptomatic carriers also carry gametocytes [20], treatment with an ACT alone would reduce gametocyte prevalence on day 7 to around 18%, and the addition of PQ at 0.75 mg/kg will further reduce the prevalence by 50% (that is, to 9%). A sample size of 300 participants per arm would have 90% power to detect this difference, at the 5% significance level, allowing for 10% of enrolees being non-compliant or lost to follow-up.

In the second hypothesis, assuming a prevalence of 9% in the standard PQ arm, 300 participants would be sufficient, with 90% power, to detect a confidence interval around the prevalence in the lower dose PQ arm below 16% and 80% power to detect that this confidence interval is entirely below 15%.

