### Statistical analysis plan

Analysis of efficacy will be on the basis of intention-to-treat. Gametocyte densities will be compared between treatment groups using one-way analysis of variance on log-transformed gametocyte densities; gametocyte carriage during follow-up will be estimated by calculating for each arm the area under the curve (AUC) of both the gametocyte density and gametocyte prevalence against time. The AUC between treatment groups will be compared using non-parametric tests. The Kaplan-Meier estimator will be used to compare gametocyte clearance times between study arms for individuals who are gametocyte positive by QT-NASBA at enrolment.

For the non-inferiority comparison between the PQ arms, the 95% confidence around the gametocyte prevalence in the PQ 0.4/0.2 mg/kg arms at day 7 will be compared to the non-inferiority limit determined by the prevalence in the PQ 0.75 mg/kg arm and delta.

For the DMFA, the proportion of infectious individuals will be compared between arms using chi-squared statistics. The proportion of infected mosquitoes will be compared between groups using mixed models to account for clustering within cages fed on blood from the same individual.

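### On a two-sided 5% test, 300 enrolled per arm gives 90% power for 18% versus 9% only with no loss; after the stated 10% allowance it is about 87%

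*Protocol article*

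**What the plan says.** The Sample size considerations section of the protocol article assumes that "treatment with an ACT alone would reduce gametocyte prevalence on day 7 to around 18" per cent, and that adding primaquine at 0.75 mg/kg halves this to 9%. It then claims: "A sample size of 300 participants per arm would have 90% power to detect this difference, at the 5% significance level, allowing for 10" per cent. That allowance covers both loss to follow-up and non-compliance.

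The number 300 is the enrolled number. The Abstract gives about 1,200 enrolled, and the Randomisation and blinding section gives equal allocation to four arms: 1,200 / 4 = 300.

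The section does not state the sidedness of the 5% level, the test, or whether a continuity correction was used. The first hypothesis is worded directionally ("results in significantly lower gametocyte carriage compared to treatment with DHA-PPQ alone"). The Statistical analysis plan section adds: "Analysis of efficacy will be on the basis of intention-to-treat".

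**The concern.** If 10% of 300 enrolled are lost, 270 remain, and the 90% should hold at 270. At the usual two-sided 5% level it holds at 300 instead, so the number printed as including the allowance equals the number needed without it.

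This is the power statement for the first hypothesis on the primary endpoint. If it is too high, a non-significant comparison of 0.75 mg/kg primaquine with control would be credited with more power than the design has. On the two-sided reading with 270 evaluable, the type II error is about 13% rather than 10%.

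**Working it through.** **Inputs.** From Sample size considerations: p1 = 0.18, p2 = 0.09, alpha = 5%, power = 90%, 300 per arm, 10% allowance. Assumed, because not stated: a two-sided test first, one-sided as the alternative; and all 10% leave the denominator, so 300 × 0.9 = 270 are analysed.

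**Step 1: the number needed (two-sided, normal approximation, pooled null variance).** With mean prevalence 0.135:

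n = [1.960 × √(2 × 0.135 × 0.865) + 1.282 × √(0.18 × 0.82 + 0.09 × 0.91)]² / 0.09²

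= [1.960 × 0.4833 + 1.282 × 0.4791]² / 0.0081 = 300.9, so **301 evaluable per arm**.

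This reproduces the plan's 300 before any loss. With 10% loss, 301 / 0.9 = 334.4, so **335 enrolled per arm**. Across the two-sided sample-size formulas tried (arcsine, unpooled, pooled, continuity-corrected), the enrolled number runs from 328 to 359.

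**Step 2: power at 300 and at 270.**

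Power = Φ{[0.09 − 1.960 × √(0.23355/n)] / √(0.2295/n)}

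- n = 300: Φ{(0.09 − 0.0547) / 0.0277} = Φ(1.277) = 89.9%
- n = 270: Φ{(0.09 − 0.0576) / 0.0292} = Φ(1.110) = 86.6%

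**Step 3: does the choice of two-sided method matter?**

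| Two-sided 5% | 300 analysed | 270 analysed |
|---|---|---|
| Normal, pooled | 89.9% | 86.6% |
| Normal, unpooled | 90.2% | 87.0% |
| Arcsine | 90.5% | 87.3% |
| Chi-squared, exact enumeration | 90.5% | 87.1% |
| Continuity-corrected | 87.6% | 83.7% |
| Fisher's exact test | 88.2% | 84.4% |

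No two-sided method reaches 90% at 270.

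**Step 4: one-sided 5%.** Replacing 1.960 by 1.645:

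- Uncorrected: power at 270 is Φ{(0.09 − 0.0484) / 0.0292} = Φ(1.428) = 92.3%. The number needed is 246, and 246 / 0.9 gives 274 enrolled.
- Continuity-corrected (0.09 reduced by 1/270): power at 270 is Φ(1.301) = 90.3%. The number needed is 267, and 267 / 0.9 gives 297 enrolled.

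The corrected one-sided version comes within three participants of the stated 300.

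**Step 5: an assumed worst case under intention-to-treat.** The allowance covers non-compliers as well as losses. Suppose that all 10% of the primaquine arm were non-compliers, stayed in the analysis and had the control prevalence. The arm's prevalence would be 0.9 × 9% + 0.1 × 18% = 9.9%. With 300 analysed, two-sided power for 18% versus 9.9% is 81.8%.

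**The case against.** The strongest reply is that the sentence can be reproduced as printed. A one-sided 5% test with continuity correction and a 10% inflation gives 297 per arm and 90.3% power at 270, and the first hypothesis is directional. The second calculation in the same section lends weak support. Treated as a two-sample comparison of 9% with 9% at one-sided 5% and 300 per arm, limits of 16% and 15% give 91% and 82%, close to the stated 90% and 80%. That is not decisive, because a one-sample exact 95% interval at 270 gives 93% and 82%.

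This reply stands as a possibility, so the 90% cannot be called wrong on every reading. It does not settle the matter. It needs two choices that the article does not state, and it needs all 10% to leave the denominator. The plain two-sided formula reaches 301 with no special choices. An unqualified 5% level is ordinarily read as two-sided. The 95% interval in the Statistical analysis plan section concerns the non-inferiority comparison and does not decide the point.

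Two further points are fair. The control rate is only approximate: with the same halving and 270 evaluable, two-sided power is 88.7% at a control prevalence of 19% and 90.4% at 20%. So the gap lies within the uncertainty of the planning assumption, though this does not make the figure right at 18%. Also, an article condenses a fuller protocol, which may name the test. Its absence here is therefore not the finding; the finding is a printed figure that does not follow on the ordinary reading.

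**Conclusion.** The point holds in conditional form. Given a two-sided 5% test, prevalences of 18% and 9%, and 270 of 300 evaluable per arm, the power is about 87% (86.6% by normal approximation, 87.1% by exact enumeration of the chi-squared test), or about 84% with continuity correction. The stated 90% corresponds to no loss. Only a one-sided 5% test supports 90% at 270.

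Three stronger readings are tempting, and the documents do not support them.

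- *The allowance was never applied.* The match between 301 and 300 suggests this, but it remains an inference while sidedness is unstated.
- *The real power is about 82%.* That figure requires every one of the 10% to be a retained non-complier with no benefit from primaquine. The article gives no split between loss and non-compliance. Its Treatment and follow-up section describes a single primaquine dose, directly observed, with one repeat possible after early vomiting. The 82% is an assumed worst case.
- *The trial is too small.* A shortfall of about 3 points does not show that, and it calls for no change in enrolment.

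**What to change.** Replace the power sentence with wording such as: *300 enrolled per arm gives about 90% power (two-sided 5%) with no loss and about 87% with 270 evaluable.* Name the test and whether a continuity correction applies. If the calculation was one-sided, say so, and say that the 90% assumes all 10% are excluded from the analysis.

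Optionally add, labelled as an assumed worst case, that two-sided power falls to about 82% if all 10% are non-compliers kept under intention-to-treat with the control prevalence.

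The cost is one or two sentences and a slightly less favourable figure. Endpoint, analysis, allocation and enrolment stay as they are.

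### Non-inferiority of the lower primaquine doses is judged by one arm's interval, which leaves out the reference arm's sampling error; with a two-sided 95% interval for the difference, the stated 90% and 80% power are not reached

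*Protocol article*

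**What the plan says.** Under Sample size considerations, the second hypothesis is that 0.4 or 0.2 mg/kg has efficacy similar to 0.75 mg/kg. Its calculation begins by "assuming a prevalence of 9% in the standard PQ arm" and states that "300 participants would be sufficient, with 90% power, to detect a confidence interval around the prevalence in the lower dose PQ arm below 16" per cent, with "80% power to detect that this confidence interval is entirely below 15" per cent. Measured from 9%, these limits imply margins of 7 and 6 percentage points.

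The first hypothesis, in the paragraph before, is sized "at the 5% significance level" and "allowing for 10% of enrolees being non-compliant or lost to follow-up". Neither phrase is repeated for the second hypothesis.

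Under Statistical analysis plan, the decision rule is that "the 95% confidence around the gametocyte prevalence in the PQ 0.4/0.2 mg/kg arms at day 7 will be compared to the non-inferiority limit". That limit is the "non-inferiority limit determined by the prevalence in the PQ 0.75 mg/kg arm and delta". The section gives no number for delta and does not say whether the interval is one- or two-sided.

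**The concern.** The hypothesis compares two randomised arms of equal size, but the interval that decides it carries the sampling error of only one. The observed 0.75 mg/kg prevalence enters the limit as if it were known. When the reference arm comes out high by chance, the limit rises with it and nothing in the interval allows for that.

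Two things are at stake. First, the false non-inferiority rate exceeds what a reader expects from a 95% interval. Second, the stated powers do not carry over to an analysis that counts both arms' error. With 270 evaluable per arm, an equally effective lower dose would then miss a 6-point margin about one time in three, where the stated 80% implies one in five. Such a miss could be misread as evidence that the lower dose is worse. The lower-dose comparison is one of the two hypotheses behind the sample size.

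**Working it through.** **Inputs.**
- Reference prevalence: 9% (Sample size considerations). The same 9% is taken for the lower-dose arm, an assumption implied by similar efficacy.
- Margins: 16 − 9 = 7 points and 15 − 9 = 6 points.
- Evaluable per arm: 300 as stated, or 300 × 0.9 = 270 if the first hypothesis's 10% loss also applies (assumption). Both are shown.
- The 95% interval is read as two-sided, so one-sided 2.5% (assumption).

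**Step 1: which calculations match the stated 90% / 80%?**

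(a) The rule as written: declare non-inferiority when the upper 95% limit for the lower-dose arm lies below the observed reference prevalence plus the margin. All pairs of binomial counts were enumerated, with both arms random at 9%.

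| Interval for the lower-dose arm | 300 per arm (7 / 6 points) | 270 per arm (7 / 6 points) |
|---|---|---|
| Wilson | 90.0% / 81.2% | 87.1% / 77.3% |
| Clopper-Pearson | 89.7% / 80.7% | 86.6% / 76.7% |
| Wald | 93.1% / 86.2% | 91.0% / 83.5% |

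(b) A two-arm comparison at one-sided 5%, power = Φ(margin / SE − 1.645), with SE = √(2 × 0.09 × 0.91 / n):
- n = 300: SE = 0.02337. Φ(2.996 − 1.645) = 91.2%; Φ(2.568 − 1.645) = 82.2%.
- n = 270: SE = 0.02463. Φ(2.842 − 1.645) = 88.4%; Φ(2.436 − 1.645) = 78.6%.

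The stated figures are thus matched by (a) at 300 with Wilson or Clopper-Pearson limits, and closely by (b).

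**Step 2: power with a two-sided 95% interval for the difference.** Wald uses Φ(margin / SE − 1.96); Newcombe is by exact enumeration.
- n = 300, 7 points: Φ(2.996 − 1.96) = 85.0%; Newcombe 84.0%.
- n = 300, 6 points: Φ(2.568 − 1.96) = 72.8%; Newcombe 71.4%.
- n = 270, 7 points: Φ(2.842 − 1.96) = 81.1%; Newcombe 80.0%.
- n = 270, 6 points: Φ(2.436 − 1.96) = 68.3%; Newcombe 67.2%.

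The Farrington-Manning score version is a little lower: 82.8% / 70.5% at 300 and 78.6% / 65.8% at 270. No variant reaches 90% / 80%.

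Evaluable numbers that would reach them, from n = (1.96 + z_power)² × 0.1638 / margin², where 0.1638 = 2 × 0.09 × 0.91:
- 90% at 7 points: (1.96 + 1.282)² × 0.1638 / 0.0049, rounded up to 352.
- 80% at 6 points: (1.96 + 0.842)² × 0.1638 / 0.0036, rounded up to 358.

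**Step 3: error rate of the one-arm rule.** Set the reference at 9% and the lower dose at 16% or 15%, so that the true difference equals the margin. The large-sample rate is Φ(−1.96 × s₂ / √(s₁² + s₂²)), with s₁² and s₂² the variances of the reference and lower-dose estimates; n cancels.
- 7 points: √(0.1344 / 0.2163) = 0.788, and Φ(−1.545) = 6.1%.
- 6 points: √(0.1275 / 0.2094) = 0.780, and Φ(−1.529) = 6.3%.

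Exact enumeration over both margins and both sample sizes gives 5.1-5.5% (Clopper-Pearson, Wilson) and 7.3-7.8% (Wald). The Newcombe interval for the difference gives about 2.5% in the same settings.

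**The case against.** The strongest defence is that the plan agrees with itself. At the stated 300 per arm, the rule it describes yields almost exactly 90% and 81%, with the reference arm allowed to vary. A two-arm calculation at one-sided 5% does about as well. Sidedness and evaluable numbers are details that an article may leave to the full protocol, and the 10% loss is written only under the first hypothesis. A shortfall appears only once a different test is substituted.

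Much of this stands. The stated powers are not shown to be an arithmetic slip, and the 270-per-arm figures are conditional. But the defence does not rescue the decision rule, which the article does fix. That rule reaches 90% / 81% by leaving out the reference arm's error, at about double the nominal error rate or more. With Wilson or Clopper-Pearson limits it also needs every participant evaluable; at 270 it gives about 87% / 77%. Wald limits hold the power at 270, but with the highest error rate (7.5-7.8%).

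A reader might infer that the powers come from a one-sample calculation with the reference fixed at 9%. The article names no formula, and 9% may be an ordinary planning assumption. Usual one-sample calculations overshoot: Clopper-Pearson gives 93.3% / 81.6% at 270 and 95.2% / 86.5% at 300. A cruder form using the variance at the limit throughout comes near at 270 (88.1% / 78.8%), but it is one candidate among several.

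**Conclusion.** The concern holds as a fault in the stated comparison and in the power that can be claimed for a proper one. Non-inferiority is decided by an interval that omits the reference arm's sampling error. Against the stated 90% / 80%, a two-sided 95% interval for the difference falls short by about 5-6 points (7-point margin) and 7-9 points (6-point margin) at 300 per arm. At 270 the shortfall is about 9-10 and 12-13 points.

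This rests on 9% in both arms and on reading the 95% interval as two-sided; the 270 figures also assume that the loss allowance carries over. If a one-sided 5% test was intended, the stated powers are about right for a two-arm comparison, but the article does not say so. The origin of the 90% and 80% cannot be settled from the article.

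**What to change.** In the Statistical analysis plan section, replace the one-arm rule: for each lower dose, compute a two-sided 95% interval for its day-7 prevalence minus that of the 0.75 mg/kg arm (for example Newcombe), and conclude non-inferiority if the upper limit is below delta. State delta as a number.

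In Sample size considerations, replace the 90% and 80% with the two-arm power at that level for the 7- and 6-point margins: about 84% and 71% with 300 evaluable per arm, or about 80% and 67% with 270. Say which evaluable number applies. Both sections must change together; otherwise power and analysis would no longer match.

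Alternatively, state openly that the test is one-sided 5% on the difference between arms, with its powers: about 91% / 82% at 300, or 88% / 79% at 270.

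Enrolment is unchanged. The cost is a revised analysis rule and, under the first option, a less favourable stated power.
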